### Recruitment and data collection

Working with HQO, we will send an invitation to all report recipients who download their report to complete a survey about the reports. We will follow an adapted Dillman protocol with a series of weekly reminders to optimize response rate [39]. Respondents will also be incentivized through a $25 raffle prize [40] provided by the research team (HQO, as a provincial agency, is prohibited from offering such incentives). Interview participants will be recruited using self-identification during the web-based surveys. Interested respondents will be contacted via e-mail to confirm interest and schedule a one-on-one, semi-structured telephone interview. An interview guide will focus on report use and ideas for improvement, prioritization of prescribing behaviour change in relation to the three prescribing indicators summarized in the report, and questions to probe the hypothesized mechanisms of action underlying the interventions (summarized in Fig. 1). It is expected interviews will last between 30 and 45 min. As interviews will focus on the experience of healthcare professionals in using feedback on aggregate data, there is very little risk of any patient-identifiable data being discussed. Nevertheless, all names and locations will be removed from transcripts to ensure that respondents are anonymous for the purposes of any reporting of results (presentations, manuscripts).

Items in the web-based survey used to measure constructs which are hypothesized antecedents of behaviour (Fig. 1) will be scored by participants using a 5-point Likert scale and described using mean and standard deviations (median and interquartile ranges in the case of skewed distributions). The survey also contains 11 items assessing regulatory focus, scored using a 9-point Likert scale, with high scores representing agreement and low scores disagreement. Six items assessed the extent of promotion focus, and five assessed the extent of prevention focus. We will assess the internal reliability of the items measuring each of the focus types (promotion/prevention) using Cronbach’s alpha. If internal consistency is <0.7, we will explore whether we can improve this by omitting individual items. We will then use the mean of the items measuring each focus type to create a composite score ranging from 1 to 9 for each focus type. The prevention focus composite score will then be subtracted from the promotion focus composite score. The resulting score will be used to classify the physicians as primarily prevention- or promotion-focused: physicians with positive scores will be classified as promotion-focused and physicians with negative scores as prevention-focused.

We will use multiple regression to explore the relationships between hypothesized predictor constructs (Fig. 1) and the dependent variable (intention to appropriately adjust prescribing) controlling for group allocation. We will then compare the post-intervention scores for the constructs across the intervention groups using independent samples *t* tests, conducting separate comparisons for each of the two main effects (message framing and professional comparator). We anticipate that approximately 250 providers will be allocated in the trial and that approximately 40% will download the Practice Reports. With an anticipated survey response rate of 40%, we expect to have 40 questionnaires available for analysis, evenly distributed between arms. With 20 survey responses in each group (presence or absence of each main intervention effect), we will have 80% power to detect a difference of 0.9 standard deviation units in any of the constructs between the two intervention arms using a two-sided *t* test at the 5% level of significance. We will use hierarchical mediation and moderation models to determine whether interventions work through hypothesized pathways to aid interpretations for generalization in various contexts. We will also conduct additional exploratory analyses to assess the impact of measurable provider, patient, and contextual characteristics on the outcomes.

The analytical method for the interviews will involve an iterative process of data collection and analysis using qualitative software NVIVO 10. Interviews will be analysed by two independent researchers using the framework method [41, 42]. This method of analysis involves six key steps: familiarization with the data, coding the data, indexing (applying the analytical framework), charting (summarizing the data from each transcript by category), and interpretation. A coding framework will be developed, with the key psychological constructs (Fig. 1) serving as overall themes. Open coding will be applied as required by the data to allow for the emergence of themes not captured within the constructs. The researchers will meet to discuss and refine the coding framework and themes. Throughout the indexing period, refinement will involve discussion with a third researcher and the wider study team as necessary, for example, to reach consensus on discrepancies and include the clinical perspective. At the charting stage, data will be re-arranged into tables and summarized according to the analytical framework. We will then re-examine the data to develop our interpretation of the mechanisms of effect of the interventions.

The framework approach ensures a systematic approach to summarizing and classifying the data, facilitating a comprehensive review of participant narratives while encouraging a higher-level conceptual analysis [42]. Using an interconnected analytic strategy allows for the constant refinement of themes while progressing towards the development of an overarching conceptual framework of how the intervention works and why. Recruitment will continue until saturation is reached; however, we anticipate conducting ~15–20 interviews based on similar studies [43]. We will employ a 10 + 3 rule, whereby at least 13 interviews will be conducted; if no additional themes are generated in the last three consecutive interviews, this will serve as evidence of data saturation. If not, interviews will continue until at least three consecutive interviews do not raise new themes. If less than 15 physicians consent to be contacted, we will contact them all for interview. Snowball sampling will be used to seek out contrasting cases, if possible.

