#### Embedded theory-based process evaluation

The process evaluation involves a mixed-methods approach informed by the UK Medical Research Council’s Guidelines [34] to examine whether the intervention targets the intended constructs outlined in the program theory (Fig. 1) and understand the contextual factors that shape how the intervention works in practice.

To assess fidelity of receipt, we will examine the extent of exposure (i.e. timing and frequency of Practice Report downloads). We propose that exposure (fidelity of receipt) will be a key effect modifier of the intervention.

The intervention’s mechanism of action will be assessed via surveys of participating physicians across all four arms to measure theoretical constructs targeted by the intervention. Targeted constructs include intention, self-efficacy, outcome expectations, descriptive norms, and goal prioritization. To minimize response burden, a single validated question was included to measure each construct for the prescription of targeted medication classes (benzodiazepines, antipsychotics, and CNS-active medications), in addition to medications that the intervention does not directly target (e.g. statins). These will therefore provide the capacity to conduct a multiple-behaviour process evaluation [35] that will examine the presumed mechanisms underlying any changes observed in prescribing and whether these vary by experimental condition. Prospect theory suggests that when physicians make a decision, they consider risky (i.e. the decision to start/stop benzodiazepines), loss-framed messages may have a larger impact on their behaviour than gain-framed messages [19, 36]. At the same time, the importance of coherence between framing and how the recipient is oriented towards promoting gains or preventing harm is emphasized in Regulatory Fit Theory [37]. We assume that most physicians are focused on preventing harm when thinking about high-risk medications. We will include a questionnaire designed to assess whether individuals are promotion- or prevention-focused which has been validated in patient population [38]; we have adapted this tool to focus on healthcare professional behaviour. Responses will we be used to assess whether respondents’ regulatory focus moderates the effect of the feedback framing intervention.

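### Process evaluation: the regulatory focus score is reduced to its sign, the only form of the moderator described; a continuous score would usually keep more information from about 40 respondents

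*Protocol article*

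**What the plan says.** Under Recruitment and data collection, the protocol article describes 11 regulatory focus items on a nine-point scale, six for promotion and five for prevention. Each set is averaged to a composite running from 1 to 9. Then: "The prevention focus composite score will then be subtracted from the promotion focus composite score". The result is used to sort respondents: "physicians with positive scores will be classified as promotion-focused and physicians with negative scores as prevention-focused".

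The purpose is given under Embedded theory-based process evaluation, where responses are to be used to assess whether respondents' "regulatory focus moderates the effect of the feedback framing intervention". The same section states: "We assume that most physicians are focused on preventing harm when thinking about high-risk medications". The analysis is named under Recruitment and data collection: "We will use hierarchical mediation and moderation models to determine whether interventions work through hypothesized pathways".

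The expected size of the survey is also there. The authors anticipate that "approximately 250 providers will be allocated in the trial and that approximately 40% will download the Practice Reports", and continue: "With an anticipated survey response rate of 40%, we expect to have 40 questionnaires available for analysis, evenly distributed between arms". The Discussion says that regulatory focus will be assessed to help interpret the trial's results.

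**The concern.** The difference score can take many values between −8 and +8. After the sign rule, a physician at +0.1 is treated the same as one at +4, and differently from one at −0.1. When a graded score is a moderator, replacing it with two groups usually weakens the interaction test, and the loss grows as the groups become less equal. Interaction tests are weak at this sample size to begin with.

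At stake is the answer to one process-evaluation question: does framing work differently according to the physician's regulatory focus? A null result from a weakened test could be read as evidence that focus does not matter. The rule also gives no class to a score of exactly zero.

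**Working it through.** **Inputs from the protocol article.** 250 providers, 40% downloading, 40% responding; 20 respondents per level of each factor; 0.9 SD, two-sided 5%, 80% power for the main-effect t tests; composites from 1 to 9; cut at zero.

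**Assumptions not in the article.** A roughly normal difference score; splits from 50:50 to 90:10; a linear framing-by-score interaction; the size of that interaction.

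**1. The article's own figures.** Respondents: 250 × 0.40 × 0.40 = 40. Power of the t test with 20 per group at 0.9 SD is 79.2% by the noncentral t with 38 df, or 81.2% by the normal approximation. Both agree with the stated 80%.

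**2. Range of the score.** Lowest 1 − 9 = −8; highest 9 − 1 = +8.

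**3. Information kept after the cut.** For a normal score cut so that a share p lies on one side, with z the normal quantile of p and φ the normal density, the squared correlation between score and class is φ(z)² / [p(1 − p)].

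| Split | φ(z) | Information kept | Lost | Equivalent of 40 |
|---|---|---|---|---|
| 50:50 | 0.399 | 0.399² / 0.25 = 0.637 | 36% | 25.5 |
| 75:25 | 0.318 | 0.318² / 0.1875 = 0.539 | 46% | 21.5 |
| 90:10 | 0.175 | 0.175² / 0.09 = 0.342 | 66% | 13.7 |

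The figures use unrounded densities. The shape of the distribution matters: at a median cut a uniform score loses 25% and a Laplace score 50%.

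**4. Power for the interaction.** Simulation with 40 respondents, 20 per framing level, residual SD 1, and a model with framing, moderator and their product. The slope makes the framing effect change by 1 residual SD per SD of score, a large effect that gives about 81% power for the continuous score.

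| Split | Continuous | Two groups |
|---|---|---|
| 50:50 | 81% | 62% |
| 75:25 | 82% | 54% |
| 90:10 | 81% | 28% |

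At 90:10 about 23% of simulated datasets had an empty cell and could not be fitted; these count as non-significant.

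**5. Smaller interactions.** At 0.5 SD per SD, power is about 30% continuous, against a little over 20% (50:50) or just under 20% (75:25) with two groups. At 0.3 SD per SD it is about 14% against about 10%.

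**6. Score of zero.** With all items kept, the means are a/6 and b/5 for whole-number totals a and b. They are equal only if 5a = 6b, so both means must be the same whole number. That happens, for instance, when someone gives the same answer throughout, but should be rare.

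**The case against.** The strongest reply has four parts.

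*No sentence says that the class enters the moderation model.* The article classifies physicians in one place, refers to responses moderating the framing effect in another, and names moderation models without giving a coding. The class could be meant for description only, and a condensed article may leave coding to the analysis plan. This stands as a limit on certainty, so the loss is conditional on the class being used. But the article does fix a classification rule and describes no other form of the variable.

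*The split is unknown.* A reader might infer from the assumption about preventing harm that the split will be lopsided, with only a handful of promotion-focused respondents. The article does not support that. Its statement gives no figure, concerns high-risk medications and not scale scores, and fits 55:45 as well as 90:10. The uneven rows above are illustrations.

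*The cut may match the theory.* Zero marks which focus dominates, and it is fixed in advance. If moderation is truly a step at that point, the class does better: with a step of 2 SD at a 50:50 split, simulated power is about 85% for the class against 60 to 64% for the score. This stands, and is a reason to keep the class as a secondary display.

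*Forty respondents is the main limit.* This also stands. A reader might infer that the cut is what makes the analysis nearly uninformative, or that a continuous score would rescue it. For moderate and small interactions neither form has adequate power.

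**Conclusion.** The point holds as a minor improvement confined to the process evaluation. The sign rule is the only form of the moderator that the article describes. If it is used in the moderation model, and the score is roughly normal with a linear interaction, it costs about 36% of the moderator's information at an even split and more at an uneven one. A loss of a third to two thirds is therefore not a fixed property of the plan: it depends on assumed splits and on the shape of the score. The power penalty is appreciable for a large linear interaction (about 81% down to 62% or 54%) and of little practical consequence for small ones. The unassigned zero is a real but small gap. A prespecified dichotomy is a legitimate choice, though usually the less efficient one. The primary and secondary prescribing outcomes and the main-effect survey comparisons do not depend on it.

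**What to change.** State in the analysis plan that the promotion-minus-prevention score enters the prespecified moderation model as a continuous variable, with a framing × score term reported as an estimate with a 95% confidence interval. Keep the promotion/prevention labels for describing respondents, or as a secondary display in case the moderation is a step, and say how a score of exactly zero is labelled. Note beside the result that about 40 respondents can detect only a large interaction, so a null finding is not read as absence of moderation.

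The cost is a few lines of wording. The items, the survey and the data are unchanged, and the Trial status section describes the intervention period as ongoing when the article was written.

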### Allocation

Cluster randomization is necessary because the intervention is delivered to physicians who may work collaboratively with other health care professionals. To prevent contamination that could occur when physicians work in multiple nursing homes, we have grouped homes that share physicians into clusters. Thus, the unit of randomization will be groups of one or more nursing homes sharing physicians. An independent statistician will randomize these clusters independently by the two factors (resulting in four experimental conditions), stratifying by total number of beds in the cluster [27], using a randomly permuted block design of length four. Physicians who sign up for the report after randomization and who belong to a cluster already assigned will be provided the same allocation as others in their group to avoid contamination.

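### The survey constructs are compared one randomised factor at a time by plain t tests, leaving the other factor in the error term; one model with both factors is a nearly free, minor improvement

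*Protocol article*

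**What the plan says.** The survey analysis is in the protocol article under Recruitment and data collection. Post-intervention construct scores are to be compared across intervention groups by "independent samples *t* tests, conducting separate comparisons for each of the two main effects (message framing and professional comparator").

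The sample size comes from a response chain. The authors expect that "approximately 250 providers will be allocated in the trial and that approximately 40% will download the Practice Reports", and then: "With an anticipated survey response rate of 40%, we expect to have 40 questionnaires available for analysis, evenly distributed between arms". The power statement is tied to the same test: "With 20 survey responses in each group (presence or absence of each main intervention effect"), there is to be "80% power to detect a difference of 0.9 standard deviation units in any of the constructs between the two intervention arms". That figure is for a two-sided test with alpha 0.05.

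The Allocation section describes an independent statistician who will "randomize these clusters independently by the two factors (resulting in four experimental conditions), stratifying by total number of beds in the cluster". Each physician who answers the survey therefore has a known, randomised level of both comparator and framing.

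Adjustment for allocation does appear in the survey analysis, but only in the separate regression of intention on the other constructs. Mediation and moderation models are planned as well, in addition to the t tests. For the primary outcome, the Analysis section promises both a four-arm and a factorial analysis; the construct comparisons are given neither.

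**The concern.** A t test on framing pools over the two comparator levels, and the reverse. If the pooled-over factor also moves the construct, its between-level difference goes into the residual variance. The interval is then wider than it needs to be, and power is lost in a comparison with only 20 per group.

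The second issue is attribution. Even numbers across the four cells are expected but not secured. Clusters are randomised, only physicians who download a report are invited, and about 40% of those are expected to answer. Nothing controls the cell sizes among some 40 respondents. If the cells are uneven, the two factors are correlated in the sample, and a one-factor t test credits the tested factor with part of the other's effect. These comparisons are meant to show which factor moved which construct, so that matters for their interpretation.

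**Working it through.** **Inputs from the protocol article (Recruitment and data collection):** 250 providers, 40% download, 40% response; 20 v 20; difference 0.9 SD; two-sided 5%. **Assumptions, not in the document:** the other factor's effect on a construct, b, taken over a range; SD = 1 within each cell; no interaction.

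**1. Reproduce the plan's figure.**
- Respondents: 250 × 0.40 × 0.40 = 40, so 20 per level of each factor.
- Standard error: √(2/20) = 0.316. Noncentrality: 0.9/0.316 = 2.85.
- Noncentral t with 38 df: power 79.2%. Normal approximation: 81.2%.

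The stated 80% lies between these and reproduces.

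**2. Even cells (10 per cell).** The two-factor additive model has residual SD 1 and 37 df, and its power is 79.1% to 79.2% whatever the value of b. The t test has the same point estimate, but its expected residual variance is 1 + (b²/4)(40/38). For b = 0.9 this is 1 + 0.2025 × 1.053 = 1.213, so the estimated SD is √1.213 = 1.10 and the interval is about 10% wider. Simulation with 100,000 replicates gives:

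| b (within-cell SD) | t test power | two-factor power | t-test interval wider by | t-test type I error |
|---|---|---|---|---|
| 0 | 79.3% | 79.2% | 0% | 5.1% |
| 0.3 | 78.6% | 79.2% | 1.2% | 4.8% |
| 0.5 | 77.4% | 79.2% | 3.2% | 4.4% |
| 0.7 | 75.6% | 79.2% | 6.3% | 3.9% |
| 0.9 | 73.1% | 79.2% | 10.1% | 3.2% |

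**3. Uneven cells.** Take an illustrative 12/8/8/12 split, which is still 20 v 20 on each factor. In one level of the tested factor 12/20 of respondents have the other factor at its upper level; in the other level 8/20 do. The t-test estimate shifts by b × (12/20 − 8/20) = 0.2b.
- b = 0.9: shift 0.18 SD. A true 0.9 reads as 1.08 or 0.72, depending on the direction of the imbalance. By simulation, t-test power is 88% or 53%, and its type I error is about 6%.
- b = 0.5: shift 0.10 SD.

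The two-factor model stays unbiased with type I error about 5%. Its power at this split is about 78%.

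**4. What the change costs if b = 0.** With even cells the loss is under 0.1 point. With cells filled at random it is about 1 point on average (79.3% to 78.2%). A realised imbalance costs somewhat more: at 12/8/8/12 the variance of the adjusted difference rises by 1/(1 − 0.2²) = 1.04, which gives the 78% above.

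**5. Adding the bed-size stratum.** The number of strata is not given. If strata are unrelated to the construct and spread at random over 40 respondents, power for 0.9 SD with b = 0 is about 78%, 76% to 77%, and 73% to 74% with 2, 3 and 5 strata, against about 79% for the planned t test.

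**The case against.** The best defence is that nothing here is stated wrongly. The power figure matches the test named, and with the even spread that the authors expect, the t test gives the same point estimate as the two-factor model and errs on the cautious side. It is a secondary survey analysis, and other models are planned on the same data. All of that stands.

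The size of the gain also rests on an assumption. The 0.9 SD is the survey's detectable difference for the factor under test; it does not predict what the other factor does. A reader might reach for the similar-effects assumption in the Power section to justify using 0.9 SD for both factors. That sentence concerns the primary outcome, where the target is 0.3 with an SD of 4, which is 0.3/4 = 0.075 SD, and at that size there is no loss. The figure linking factors to constructs is not available here, so it cannot be checked whether both factors target the same construct.

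The document also does not say which SD the 0.9 refers to. If it is the SD pooled over the other factor, the planned t test keeps at least its stated power. The two-factor model would still do better: about 82% at b = 0.5 and 87% at b = 0.9.

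What the defence does not remove is the dependence on even cells, which the recruitment route does not secure, or the fact that the alternative costs almost nothing.

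**Conclusion.** The point holds as a minor improvement to the process evaluation. The separate t tests leave the other randomised factor in the error term. With even cells and within-cell SD, the loss is about 6 points of power if that factor's effect is 0.9 SD, about 2 points at 0.5 SD, and under 1 point at 0.3 SD or below. With uneven cells the estimate shifts by the other factor's effect times the imbalance, for example 0.18 SD at 12/8/8/12 and 0.9 SD.

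Three stronger readings are not supported. The 80% power is not miscalculated. The t test is not invalid or biased in the balanced case that the plan expects; there its type I error is at or below about 5%. A loss as large as 8 points, reached by setting a t-test power for randomly mixed cells against a two-factor power for even cells, is not a like-for-like comparison; like for like, the loss at 0.9 SD is 6 to 7 points.

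All sizes depend on the assumed effect of the other factor and on no interaction. No primary or secondary trial outcome is affected.

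**What to change.** Under Recruitment and data collection, replace the separate t tests with one linear model per construct that contains both randomised factors, comparator and framing. Report each factor's adjusted mean difference with its 95% confidence interval. State that the 80% power at 0.9 SD refers to the within-cell SD.

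Do not require the bed-size stratum in this model. The number of strata is not given, and with about 40 respondents the extra terms can cost more power than the second factor recovers.

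The cost is a wording change and one degree of freedom (37 instead of 38). Allocation is already known for every respondent, so no new data are needed. If the other factor has no effect, the price is under 0.1 point of power with even cells and about 1 point on average when cells fall at random.
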